#### Statistical power and sample size considerations

Statistical power was calculated to ensure sufficient sample size to address two key components of study aims: detect an omnibus effect on the primary outcome of PEI scores across three intervention conditions, against the null hypothesis that providers’ assistance behaviors are equal across intervention conditions; and detect the differences in provider assistance rates (*e.g.*, Quitline referral).

For the primary outcome of provider assistance behaviors, prior data from a recent clinical trial conducted to improve treatment of tobacco dependence in primary care was obtained [78,79]. The investigators compared Intervention (a provider training and practice facilitation program similar to ours) with Usual Care. The Intervention group reported an average PEI provider assistance score of 8.40 (SD = 1.93) versus an average of 6.24 (SD = 2.12) in the Usual Care group, which translates to an estimated effect size of 1.02 (using the larger SD = 2.12). Using this 1.02 effect size, we estimated an 86% statistical power to detect such an effect at a two-sided Type-I error rate of 0.01 (to control for multiple comparisons) for 18 sites (six sites randomized to each intervention condition) and 100 post-intervention patients per site [80].

Statistical power was also estimated for provider assistance behaviors in a generalized estimating equation (GEE) approach. Bentz *et al.*[23] reported that 10.5% of providers randomized to the control condition gave active assistance (*e.g.*, referrals to quitlines); and 20.1% of providers randomized to their feedback condition gave active assistance. Roski *et al.*[33] reported a 31.4% cessation assistance rate for sites randomized to a provider incentive condition. Hence, provider assistance rates are estimated to be 10%, 20%, and 30% (rounded to the nearest decimal point) for the CBP, CBP + PF, and CBP + PF + P4P arms, respectively. Horton’s simulation method [81] was applied to calculate the statistical power of a logistic GEE model. The simulated statistical power was 82% statistical power to detect a 20% versus 10% difference in a GEE model comparing CBP + PF versus CBP alone. The corresponding statistical power for the 30% versus 20% difference between CBP + PF + P4P and CBP + PF is 73%. The statistical power for the larger 30% versus 10% difference between CBP + PF + P4P and CBP alone is 97%. Other parameters in the simulations included a two-sided Type-I error rate of 0.01 to control for multiple comparisons and an intra-class correlation of 0.22, in prior work [23] that closely resembles our trial design.

Using the indicators described in the evaluation plan (See Table 3), relevant process data describing the implementation fidelity of the intervention strategies (CBP, PF, and PFP) will be summarized. All reporting of trial outcomes data will be consistent with cluster randomized CONSORT guidelines [82].

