The central hypothesis is that the value of these promising implementation strategies is additive and that instituting all three strategies (CBP, PF, and P4P) will be superior to CBP alone and CBP + PF in increasing delivery of cessation assistance to smokers. The ultimate goal is to provide critical new knowledge to facilitate the widespread implementation, dissemination and sustained utilization of evidence-based tobacco use treatment strategies in dental practices.

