#### MLM approach to address the primary aim

A two-level MLM will test of the effectiveness of the implementation strategies. The primary outcome is the summary score of the PEI assessment of provider assistance (score range 0 – 8). At level one, we will enter each patient’s PEI score of dental provider assistance as a function of intervention and time (pre and post intervention), thereby allowing each site to serve as its own pre-implementation control, an added benefit to minimize an order effect, (*e.g.*, sites that enter the active implementation phase later may derive greater benefits due in part to improved efficiency in logistics coordination) [75-77]. Additional covariates may also be included (*e.g.*, patients’ age, gender, and education).

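### The primary PEI score is powered for an omnibus test of equal arms, but the central hypothesis is that arm three beats each of the other two arms

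*Protocol article*

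**What the plan says.** The central hypothesis closes the Background section of the Protocol article and is repeated in the abstract: "instituting all three strategies (CBP, PF, and P4P) will be superior to CBP alone and CBP + PF". That is two directional comparisons.

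Under Statistical power and sample size considerations, the first of two targets is to "detect an omnibus effect on the primary outcome of PEI scores across three intervention conditions". The article frames this test as one "against the null hypothesis that providers’ assistance behaviors are equal across intervention conditions". The level is a "two-sided Type-I error rate of 0.01 (to control for multiple comparisons"), and the stated power is 86% for an effect size of 1.02 with six sites per arm and 100 post-intervention patients per site. The section on the MLM approach models "each patient’s PEI score of dental provider assistance as a function of intervention and time (pre and post intervention") and names no contrast between arms.

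The second target is assistance rates. Here all three pairs are powered: 82% for CBP + PF against CBP, 73% for P4P against CBP + PF, and 97% for P4P against CBP. The settings are "a two-sided Type-I error rate of 0.01 to control for multiple comparisons and an intra-class correlation of 0.22". Neither place gives the number of comparisons or the familywise level behind 0.01.

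**The concern.** The null hypothesis set for the primary outcome is not the one that the central hypothesis needs to reject. Equality of three arms is false as soon as any arm differs. If feedback works and payment adds nothing, the omnibus test should reject, and yet the claim about arm three would be wrong. Whether payment adds to feedback is the reason for having a third arm, and on the PEI score the article gives neither a test nor a power figure for it.

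The level matters as well. With 18 sites there is little power to spare, and 0.01 may be stricter than the hypothesis requires, depending on which tests it was meant to cover.

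**Working it through.** **Inputs.** Six sites per arm, 100 post-intervention patients per site, two-sided 0.01, effect size 1.02. The effect size comes from "an average PEI provider assistance score of 8.40 (SD = 1.93) versus an average of 6.24 (SD = 2.12"): (8.40 − 6.24)/2.12 = 1.019. No ICC is given for the PEI score. I take 0.22 from the assistance-rate calculation as an assumption and also show 0.10.

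**Reproducing the 86%.** Design effect 1 + 99 × 0.22 = 22.78. Effective n per arm 600/22.78 = 26.3. Power = Φ(1.02 × √(26.3/2) − 2.576) = Φ(3.70 − 2.576) = 87.0%, and exactly 86% at ICC 0.226. So the stated figure is what a two-arm normal approximation gives.

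**Omnibus test with the same inputs.** Variance of a site mean in SD units: 0.22 + 0.78/100 = 0.2278. Noncentrality λ = 6 × Σ(μ − mean)²/0.2278, with F on 2 and 15 df and critical value 6.36 at 0.01.

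| Arm means (one, two, three) | λ | Power at 0.01 |
|---|---|---|
| 0, 0, 1.02 or 0, 1.02, 1.02 | 18.27 | 77% |
| 0, 0.51, 1.02 | 13.70 | 61% |

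The article does not say which arms the 1.02 separates. If each added strategy were worth 1.02 (means 0, 1.02, 2.04), omnibus power would be close to 100%. The claim about arm three would still rest on arm three v arm two, which has 76% power at 0.01 and 93% at 0.05.

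**What the omnibus can and cannot show.** With means 0, 1.02, 1.02, where payment adds nothing, the omnibus test at 0.01 rejects 77% of the time. A test of arm three v arm two at 0.01 after that rejection is positive about 1% of the time. The omnibus result carries no information on the payment question; the pairwise test does.

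**Power for the hypothesis itself.** Simulated site means (400,000 replicates), pooled variance, 15 df, both arm-three contrasts rejected in arm three's favour:

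| ICC | Arm means | Each contrast at 0.01 | Closed procedure, 0.05 |
|---|---|---|---|
| 0.22 | 0, 0, 1.02 | 65% | 88% |
| 0.22 | 0, 0.51, 1.02 | 17% | 40% |
| 0.10 | 0, 0, 1.02 | 97% | 99.8% |
| 0.10 | 0, 0.51, 1.02 | 42% | 70% |

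Testing both contrasts at 0.05 without the omnibus gate gives the same figures to within one percentage point.

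**The 0.01 level.** If it covers three PEI pairs at 5% familywise, Bonferroni would allow 0.05/3 = 0.0167. Three pairs at 0.01 have a simulated familywise error of 2.6%. The closed procedure, omnibus at 0.05 and then each pair at 0.05, has 5.0% under equal arms. If it covers three pairs on two outcomes, Bonferroni would need 0.05/6 = 0.0083, and 0.01 would be slightly lenient. A level of 0.01 corresponds to 0.05/5.

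**The case against.** The omnibus test is not the whole plan. The authors clearly had pairs in mind: they power all three on assistance rates, and a correction for multiple comparisons makes sense only if more than one test is intended. Aim 1 is to compare three strategies, and an omnibus test fits that aim. The analysis paragraph names no omnibus test, and contrasts and testing order are often left to an analysis plan. All of this is fair, and it means the article should not be read as ignoring pairwise comparisons. It does not close the gap: the article itself states which null the primary outcome is powered against, and that null does not correspond to the central hypothesis.

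Two stronger readings are tempting, and the document supports neither. A reader might take the 77% as a false-positive rate. It is not: when feedback works, the arms do differ, and rejecting equality is correct. A reader might also say that 0.01 plainly over-corrects. That presumes a family of three tests at 5%, which the article never states; with six tests it would not over-correct. A conservative level is also a legitimate choice.

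The size of the gain is open to challenge too. The ICC is borrowed from another outcome, and the simulation uses post-intervention means only, while the planned model also uses baseline data. Against plain Bonferroni at 0.0167 the joint claim moves only from 65% to 74%, or from 17% to 23%. Most of the gain comes from matching the test to the hypothesis.

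**Conclusion.** The point holds as a mismatch between hypothesis and test on the primary outcome. No PEI test or power figure in the article addresses whether arm three beats both others, and the 86% offered for the omnibus effect is a two-arm figure. The planned 0.01 level costs about 23 percentage points of power for the joint claim at ICC 0.22 under either mean pattern. At ICC 0.10 it costs about 3 points for means 0, 0, 1.02 and about 28 for 0, 0.51, 1.02. These sizes rest on post-intervention site means, 15 df, the assumed ICC and the assumed mean patterns; they are not powers of the planned pre-post model. The criticism of the level is conditional on 0.01 being meant for three PEI pairs at 5% familywise.

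**What to change.** - Make arm three v arm one and arm three v arm two on the PEI score the confirmatory contrasts. Claim the central hypothesis only if both are rejected at two-sided 0.05 in favour of arm three. A claim that requires both rejections (intersection-union) needs no multiplicity correction.
- If single pairs, including CBP + PF v CBP, are also to be claimed, use the closed three-arm procedure: omnibus at 0.05, then each pair at 0.05. It holds 5% familywise error within the PEI outcome.
- State which tests and which familywise level 0.01 was meant to cover, or withdraw it for the PEI score. Rank assistance rates as a separate outcome below the PEI score.
- Restate power for the two PEI contrasts, with the assumed ICC, a range for it, and the arm means.

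The cost is wording and a new power calculation; sites and data collection do not change. The price is a less strict level for each contrast, and no control of error across the two outcomes unless they are ranked. The Trial status section has the first wave still in its implementation period, so at that stage the change could precede post-intervention interviews.

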### Outcome evaluation (aim one)

#### Primary outcome

To assess the primary outcome of provider adherence to tobacco use treatment guidelines, we will conduct and compare pre- and post-intervention patient exit interviews conducted with eligible smokers at each of the 18 clinic sites. Prior to beginning of the implementation intervention, we will conduct 100 patient exit interviews (n = 1,800 pre-intervention) at each clinic site. Then, after each site has completed the planned intervention, another independent sample of 100 smokers will complete patient exit interviews (n = 1,800 post-intervention). Patient interviews conducted at the point of service are considered to be the optimal non-observational method for measuring provider delivery of outpatient treatment [58,59]. A modified patient exit interview (PEI) [60] will be used as a brief patient-reported measurement tool for the assessment of provider delivery of tobacco use screening and treatment. A PEI index (summary) score is determined by adding the number of tobacco treatment behaviors each patient reports that the provider implemented during the most recent visit. PEI index will scores range from 0 to 8. The questions assess the full spectrum of PHS guideline recommended care (*i.e.*, 5As). For example, patients are asked if their provider advised them to quit, offered cessation counseling and/or discussed cessation medications. The PEI has well-established validity as evidenced by strong correlation with more costly audio-taped assessment of physician-patient interactions (r = 0.67, p < 0.001) and has been commonly used to accurately measure providers’ delivery of tobacco cessation assistance efforts during office practice, and to monitor providers’ adherence to tobacco cessation treatment guidelines in clinical trials. Prior to and approximately nine months following each site’s enrollment, consecutive patients will be approached during their clinic visits by trained research study assistants (RSA), to determine current smoking status and to obtain consent for the PEI. Patient eligibility will include those: age 18 or over; English- or Spanish-speaking; current smokers defined as those who report smoking within the past seven days; New York State residents; and who have an appointment with a dentist or hygienist for routine non-emergent care. Immediately after their dental visit, patients will complete the PEI to assess provider adherence to the PHS Guideline (5As). We expect that most surveys will be administered using a computer tablet with a password protected, web-based data entry portal (REDCap) [61]; however, paper surveys will be available, as needed.

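### The 86% power for the primary PEI outcome rests on a training-versus-usual-care effect of 1.02, a contrast that none of the three arms provides

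*Protocol article*

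**What the plan says.** Under *Statistical power and sample size considerations*, the protocol article gives the purpose of the primary calculation as to "detect an omnibus effect on the primary outcome of PEI scores across three intervention conditions", against a null of equal conditions.

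The effect comes from a primary care trial: "The investigators compared Intervention (a provider training and practice facilitation program similar to ours) with Usual Care". Mean scores there were 8.40 (SD 1.93) with the programme and 6.24 (SD 2.12) without it. The article turns this gap into a standardised difference, "which translates to an estimated effect size of 1.02 (using the larger SD = 2.12". The stated power is 86% at two-sided alpha 0.01, with six sites per arm and 100 post-intervention patients per site. No ICC is given for this calculation. The ICC of 0.22 in the same section belongs to the simulations for the binary assistance rate.

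Elsewhere, *Primary outcome* states "PEI index will scores range from 0 to 8", and *MLM approach to address the primary aim* repeats that range. Table 2 and *Arm one: staff training and CBP* give training and CBP to every site. The central hypothesis, at the end of *Background*, is that the full package is superior to CBP alone and to CBP + PF.

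**The concern.** A power figure informs a design only if its effect size belongs to a contrast the design tests. By the article's own description, the source intervention resembles CBP. If CBP moved PEI scores by about one SD over usual care, all three arms would share that gain and it would drop out of every between-arm comparison. The hypotheses concern what PF and P4P add on top, and no PEI effect is given for either.

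Two further mismatches sit in the same paragraph. The announced test is a three-arm omnibus test, but the input is one two-group difference with no set of three means. And a mean of 8.40 cannot occur on a 0-8 score, so the source score is not this trial's score.

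At stake is the only power statement for the primary outcome. A reader would take from it that 18 clinics suffice to separate the arms on PEI score.

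**Working it through.** **Inputs from the article:** means 8.40 and 6.24, larger SD 2.12; 6 sites per arm; 100 post-intervention patients per site; two-sided alpha 0.01.
**Assumed:** the ICC. The value 0.22 is borrowed from the binary outcome; 0.05 and 0.10 are added to show a range.

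**1. Effect size.** (8.40 - 6.24)/2.12 = 2.16/2.12 = 1.02. The article's figure is correct.

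**2. Stated power.** The standard error of a pairwise difference in SD units, post-intervention data only, is SE = sqrt(2 × [ICC + (1 - ICC)/100]/6). At ICC 0.22, SE = sqrt(2 × 0.2278/6) = 0.2756, and 1.02/0.2756 = 3.70. With normal critical value 2.576, power is 87%, close to the stated 86%.

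**3. Same effect, other methods, ICC 0.22.**

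| Method | Power at d = 1.02 |
|---|---|
| Two arms, normal approximation | 87% |
| Two arms, noncentral t, 15 df | 76% |
| Two arms, noncentral t, 10 df | 69% |
| Omnibus F(2,15), means 0, 0, 1.02 | 77% |
| Omnibus F(2,15), means 0, 0.51, 1.02 | 61% |

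The omnibus noncentrality is the sum of squared deviations of the arm means divided by (0.2278/6). For 0, 0.51, 1.02 it is 0.5202/0.03797 = 13.7; for 0, 0, 1.02 it is 0.6936/0.03797 = 18.3.

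**4. Which ICC returns exactly 86% at d = 1.02?** Normal approximation 0.226; t on 15 df 0.175; t on 10 df 0.152; omnibus F 0.182 (two arms equal) or 0.134 (middle arm halfway). Several routes reach the figure, so the method cannot be inferred from it.

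**5. Increments smaller than 1.02.** The article gives no PEI effect for PF or P4P, so the d values are assumptions. Pairwise, post-only, alpha 0.01, noncentral t on 15 df:

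| ICC | SE | Power, d = 0.5 | d detectable with 80% power |
|---|---|---|---|
| 0.05 | 0.141 | 72% | 0.54 |
| 0.10 | 0.191 | 41% | 0.73 |
| 0.22 | 0.276 | 17% | 1.06 |

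**6. Scale.** The source mean of 8.40 exceeds the maximum of 8 by 0.40. No rescaling is described.

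**The case against.** Several points on the other side stand.

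- **No miscalculation is shown.** A reader might infer that the 86% came from ignoring the small number of sites. Step 4 shows that methods with site-level degrees of freedom also reach 86% at a lower ICC. The method reference is not at hand, and an ICC left out of a condensed article is not in itself a fault.
- **The scale mismatch does not void 1.02.** A standardised effect can be carried between scales. One might go further and argue that from 6.24 only 1.76 points, or 0.83 SD, remain below 8. That places a mean from a different scale on this one and is not supported. The pilot rates in *Performance feedback (PF)* (28% advice and 7% assistance before implementation) suggest ample room to rise.
- **The 10%, 20% and 30% planning rates are not PEI effects.** They describe one binary behaviour. Converting them gives about 0.28 and 0.23 between adjacent arms by Cohen's h, but 0.45 and 0.30 by logit scaling, and neither leads to a summed 0-8 score.
- **The arm contrasts are not without any power statement.** The same section gives 82%, 73% and 97% for the three pairwise comparisons of assistance rates.
- **The planned model uses baseline data.** Post-only figures are therefore not the power of the planned analysis.

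A pre-post change within the CBP arm would also resemble the source contrast, but the section says it powers a difference across conditions. None of these points supplies a PEI effect for PF or P4P over CBP, so the main point is untouched.

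**Conclusion.** The 86% is a sound calculation for a comparison this trial does not make. It should not stand as the power for the between-arm hypotheses on the primary outcome. This follows from the article's own description of the source trial and of its arms, and depends on no assumed ICC.

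The size of the problem does depend on assumptions. For an increment of 0.5 SD, post-only power runs from about 17% (ICC 0.22) to 72% (ICC 0.05), before a gain from baseline data that cannot be computed from the article. A reader might conclude that the trial is underpowered. The article does not establish that, because it gives neither the expected PEI increment nor an ICC for the PEI. What it establishes is that adequate power for the primary outcome has not been shown.

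**What to change.** Rewrite one paragraph.

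- Withdraw the 86% as the power for this trial's between-arm comparisons.
- State the minimum detectable PEI difference for the pairwise arm contrasts, in SD units and in points on the 0-8 scale, using site-level degrees of freedom.
- State the omnibus power under a written-out set of three arm means.
- Show both over a stated range of ICC and of site-level pre-post correlation.
- Say how the source score relates to the 0-8 score, or drop the source figures.

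The completed wave-one baseline interviews can inform the PEI SD. They cannot supply the ICC: with three clinics of 100 patients and an estimate of 0.22, the 95% interval from the one-way F ratio (1 + 100 × 0.22/0.78 = 29.2 on 2 and 297 df) is about 0.06 to 0.92.

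The number of sites and patients does not change. The cost is that the stated figure becomes less favourable.

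### With six sites per arm, an uncorrected logistic GEE would test assistance rates at about 4-8% rather than the stated 1%, and the protocol names no small-sample correction

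*Protocol article*

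**What the plan says.** The section Statistical power and sample size considerations gives two targets for power: an omnibus effect on the PEI score, and differences between arms in assistance rates. For the second, it reports that a "simulation method [81] was applied to calculate the statistical power of a logistic GEE model". Planning rates are 10%, 20% and 30% for CBP, CBP + PF and CBP + PF + P4P, and each pair of arms is contrasted. The simulation settings include "a two-sided Type-I error rate of 0.01 to control for multiple comparisons and an intra-class correlation of 0.22". The design, given in the preceding paragraph of that section, is "18 sites (six sites randomized to each intervention condition) and 100 post-intervention patients per site".

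The article does not say whether the GEE standard errors are robust or model-based, whether a normal or t reference is used, or whether a correction for few clusters is made. The primary outcome is handled differently: under MLM approach to address the primary aim, the 0-8 PEI summary score is tested in a two-level multi-level model.

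**The concern.** Each pairwise contrast rests on 12 sites. The usual GEE sandwich variance, referred to a normal distribution, relies on a large number of clusters. With six per arm the variance is biased low, and the normal critical value ignores the uncertainty in it. Low assistance rates combined with a high intra-class correlation make this worse, because site proportions are then strongly skewed. Those are the planning conditions for the CBP arm.

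The 0.01 level was chosen to allow for multiple comparisons. If the test rejects several times as often under the null, that allowance is lost. A chance difference in assistance between strategies could then be read as support for adding feedback or payment.

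**Working it through.** **Inputs.** From the power section: k = 6 sites per arm, m = 100 post-intervention patients per site, two-sided level 0.01, intra-class correlation (ICC) 0.22, and rates of 10%, 20% and 30%. Assumed here, because the article is silent: an uncorrected sandwich variance, a normal reference, and each planning rate in turn as the common null rate.

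**1. The plan's own figures.** Three contrasts at 0.01 carry at most 3 × 0.01 = 3% overall. The stated powers are 82%, 73% and 97%. At ICC 0.22 the design effect is 1 + 99 × 0.22 = 22.78, so the effective size per arm is 600 / 22.78 = 26.3. The two-proportion formula then gives 5.8%, 4.0% and 21.6%. A simulated GEE with the uncorrected test gives about 18%, 11% and 38%. The stated powers do not reproduce. That is a separate fault, and the lack of a small-sample correction does not explain it.

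**2. The test.** With equal cluster sizes and a site-level arm, the GEE has a closed form:

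- estimate = logit(p̄₁) − logit(p̄₀)
- variance = sum over the two arms of [Σ(pᵢ − p̄)² / k²] / [p̄(1 − p̄)]²

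Here pᵢ are site proportions and p̄ is their arm mean. On a test data set this matched standard GEE software in estimate and standard error, under both independence and exchangeable working correlation.

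**3. Analytic check.** The divisor k² replaces k(k − 1), so the variance is low on average by a factor of 5/6. If site proportions were normal, the test would reject when |t| on 10 df exceeds 2.576 × √(5/6) = 2.352. The probability of that is 4.05%, before any effect of skewness.

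**4. Simulated false-positive rate at nominal 1%** (ICC 0.22, beta-binomial sites, 200,000 two-arm trials per setting; first four rows):

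| Test | 10% | 20% | 30% |
|---|---|---|---|
| Uncorrected sandwich, normal reference | 8.3% | 5.1% | 4.2% |
| Kauermann-Carroll, variance × 6/5, t on 10 df | 2.8% | 1.4% | 1.0% |
| Mancl-DeRouen type, variance × (6/5)², t on 10 df | 1.8% | 0.85% | 0.6% |
| Unadjusted t-test on 12 site proportions, 10 df | 0.4% | 0.8% | 1.1% |
| 18-site regression on arm and baseline proportion, 14 df | 0.7-1.1% across settings | | |

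**5. Sensitivity of the uncorrected test.**

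- ICC from 0.01 to 0.10: 3.9% to 5.4%.
- Logit-normal site effects at ICC 0.22: 8.8%, 5.6% and 4.5%.
- Pre/post arm-by-time GEE at ICC 0.22, with site autocorrelation assumed to be 0.5 or 0.8: about 10-11%, 6.4% and 5.0%.

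**6. All three contrasts together.** In a three-arm null simulation, the chance of at least one false claim was 18.6%, 12.1% and 10.0% with the uncorrected test, against the intended ceiling of 3%. With site-level t-tests it was 1.1%, 2.3% and 2.9%.

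**The case against.** The strongest reply is that the article commits to no particular standard error. GEE appears only in the power paragraph and the abbreviation list. The section General approach names multi-level models as the paradigm for outcomes. Variance estimators and degrees of freedom are usually settled in an analysis plan or full protocol, and neither is shown. This stands. A reader might infer that the plan rejects a small-sample correction, or that the trial's error rate is 4-8%. The text supports neither: it states no correction and rules none out.

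A reader might also infer that the primary result is affected. The documents do not support that. The primary PEI score has its own two-level model, the binary assistance rate is not listed as a primary or secondary outcome, and these simulations say nothing about the size of the multi-level test.

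What remains is that the article ties the assistance-rate contrasts, one of its two powered components, to a named method, a number of clusters and an error level. The ordinary form of that method does not deliver that level with 12 clusters. The remedy is not free of difficulty either: a Mancl-DeRouen-type correction still exceeds 1% at the 10% rate, and the unadjusted site-level t-test is conservative there.

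**Conclusion.** The point holds in conditional form. If the assistance-rate contrasts are analysed by logistic GEE with uncorrected robust standard errors and a normal reference, the test at the stated 1% runs at about 8%, 5% and 4% for common rates of 10%, 20% and 30% at ICC 0.22. The excess does not depend on that ICC: the rate stays near 4-5% for values from 0.01 to 0.10. The result rests on six equal sites of 100 per arm, beta-binomial variation between sites and a post-intervention comparison; the alternatives tried gave similar or higher rates. It bears on a powered secondary analysis and leaves the primary test untouched.

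**What to change.** State the test for assistance rates before the data are analysed.

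- **Preferred:** a site-level regression of the post-intervention proportion on arm and the site's own baseline proportion, with t tests for pairs and an F test overall. Eighteen sites less four coefficients (intercept, two arm terms, baseline) leave 14 residual degrees of freedom. The baseline exit interviews, 100 per site, already supply the covariate.
- **If GEE is kept:** name a bias-corrected sandwich estimator and a t reference, and show by simulation that the test holds its size at a 10% rate and ICC 0.22. Kauermann-Carroll with 10 df (about 2.8%) and a Mancl-DeRouen-type correction (about 1.8%) do not reach 1% there, so naming a correction is not enough.
- **Power:** compute any restated power with the same test.

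The wording change is small and needs no new data. The price is wider intervals and lower power. At ICC 0.22 the Kauermann-Carroll test with 10 df has power of only about 8%, 4% and 20% for the 20% v 10%, 30% v 20% and 30% v 10% contrasts. Baseline adjustment may recover some of this, by an amount that depends on the correlation between a site's two periods, which the article does not give.
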